**Contact details**

[name]

Department of Rheumatology, Third Affiliated Hospital of Sun Yat-sen University

[name]

Telephone numbers: [name]

Trial Protocol

1.Introduction

A number of studies have demonstrated the efficacy of tumor necrosis factor-α inhibitors (TNFi) in reducing inflammation of Sacroiliac Joints (SIJ) and Spine in ankylosing spondylitis (AS) patients. However, the effect of TNFi on retarding radiographic progression in AS patients is still controversial. Interestingly, one clinical trial reported that a strategy of continuous use of NSAIDs (celecoxib) reduced radiographic progression in symptomatic patients with AS. The underlying mechanism is still unknown. It is possible that while the TNFi control inflammation very effectively, it does not have much effect on retarding new bone formation. The NSAIDs on the other hand may not be as effective in controlling inflammation but do inhibit the pathogenic processes involved in bone changes that occur in AS patients. So AS patients may have a better outcome (both control of inflammation and structural changes) if treated with a combination of NSAID and TNFi. This study is designed to assess the clinical and structural outcomes in AS patients treated with a combination of an NSAID (celecoxib) + TNFi (etanercept) versus celecoxib or etanercept alone.

2.Study objective and outcomes

2.1 Objectives

This study is designed to evaluate the effect of celecoxib and/or etanercept treatment on clinical and structural changes in active AS patients after 52 weeks as measured by clinical, MRI and radiographic assessments. The structural changes seen by MRI and radiographic measures will also be compared and correlated. The safety information will also be collected and analyzed during the study. The safety information includes adverse event (AE), serious adverse event (SAE) and clinically significant abnormal laboratory tests.

2.2 Outcomes

There are two primary outcomes in this study. The first one is to compare the Spondyloarthritis Research Consortium of Canada (SPARCC) score of SIJ and spine from baseline to week 52 in three treatment groups in active AS patients. The co-primary outcome is to compare the Assessment of Spondyloarthritis International Society (ASAS) 20 response rate of three treatment groups at week 52.

Secondary outcomes include ASAS40, ASAS70, ASAS5/6 response rate, ASAS partial remission, Ankylosing Spondylitis Disease Activity Score (ASDAS) remission and ASDAS low disease activity, Bath Ankylosing Spondylitis Disease Activity Index (BASDAI), Bath Ankylosing Spondylitis Functional Index (BASFI), Bath Ankylosing Spondylitis Metroloty Index (BASMI), Masstricht Ankylosing Spondylitis Enthesitis Score (MASES) and safety outcomes.

3.Study design

This is a prospective, open label, active controlled, parallel group study. A total of 150 active AS patients will be randomized in a 1:1:1 ratio into the following three treatment groups: celecoxib 200mg twice a day, etanercept 50mg weekly, celecoxib 200mg twice a day plus etanercept 50mg weekly for 52 weeks. This study will be registered in the Clinical Trials.

4.Subject Selection

4.1 Inclusion Criteria

Patients are eligible to be included in the study only if they meet all of the following criteria at screening or as specified:

[1] Subject is 18-65 years old at the screening age.

[2] Subject meets 1984 modified New York criteria of ankylosing spondylitis (AS) diagnosis (have unilateral sacroiliitis grade 3-4 or bilateral sacroiliitis grade 2-4, plus at least one of the following three clinical criteria: a. low back pain last more than 3 months, improved with exercise but not with rest. b. limitation of lumbar spine movement in sagittal and frontal planes. c. chest expansion decreased relative to normal values for age and sex.).

[3] Subject has active AS defined as the following three aspects: BASDAI≥4 or ASDAS score ≥2.1; CRP>6mg/L or ESR >28mm/1^st^ hour;

[4] Subject has sydesmophytes ≥2 and <16 measured by X-ray from cervical to lumbar spine;

[5] Fertile women must agree and commit to use a medically accepted form of contraception during the study and for at least 12 weeks after the last dose of test article;

[6] No evidence of active or latent or inadequately treated infection with Mycobacterium tuberculosis.

4.2 Exclusion Criteria

[1] Pregnant women.

[2] Subject has a history of infection requiring hospitalization and parenteral anti-microbial, or otherwise judged clinically significant by the investigator within the 24 weeks prior to screening.

[3] Subject is receiving TB chemoprophylaxis during screening and has had ALT and /or AST >2-times the upper limit of normal during this period.

[4] Subject has received a TNFi or other biologics within 12 weeks prior to screening.

[5] Subject has parenteral or intra-articular injections of corticosteroids within 12 weeks prior to screening.

[6] Subject has psoriasis or IBD.

[7] Subject has diabetes with uncontrolled hypoglycemia.

[8] Subject has a history of hypersensitivity to any of the study medications and sulfonamides or components of the concomitant medicines.

[9] Subject has a history of asthma, urticarial, or other allergic-type reactions after taking aspirin or other NSAIDs.

[10] Subject has a history of cancer or lymphoproliferative disease.

[11] Subject has a history of psychiatric disease, intellectual deficiency, poor motivation or other conditions that will limit the validity of informed consent to participate in the study or the potential compliance to study procedures.

[12] Subject has a history of alcohol or drug abuse that would interfere with the subject’s ability to comply with protocol requirements.

[13] Subject currently or recently has a history of uncontrolled clinically significant disease including gastrointestinal ulcer, active gastrointestinal bleeding, myocardial infarction within 12 months, unstable angina pectoris, congestive heart failure, cardiac surgery and the perioperative period in the setting of coronary artery bypass graft surgery.

[14] Study investigators, sub-investigators, study coordinators, employees of a participating investigator or immediate family members of the aforementioned are excluded from participating in this study.

5.Study treatments

5.1 Allocation to treatment

Patient eligibility will be determined at the screening and baseline visits, at which time the patient will be randomized (defined as the process of receiving medication and randomization number from SPSS v 17.0).

5.2 Preparation and Dispensing

Injections should never be administered consecutively in the same location. Instead, alternate sites (left and right arms, left and right thighs, left and right sides of the abdomen) should be used with each administration. New injections should be given at least 1 inch from the old sites and never into areas where the skin is tender, bruised, red, or hard.

5.3 Concomitant medication

During the study a stable dose of sulfasalazine or methotrexate for AS will be allowed. Doses of such concomitant medications should remain stable 12 weeks prior to study and during the study. NSAIDs (except celecoxib) and corticosteroids are prohibited during the study. NSAIDs should be stopped 7 days or 5 half-lives (whichever is longer); oral corticosteroids should be stopped 4 weeks prior to administration of study drugs. Aspirin 75 mg per day for cardiovascular protection is allowed. Proton pump inhibitors (PPIs) should be considered for patients treated with celecoxib and with GI risk. Concomitant medication can be stopped or adjust dosage for safety reason in the discretion of investigator. All adverse events related with the concomitant medicine should be recorded.

6.Study procedures

Timetable and measures to be made

|  | screen | Week 0 | Week 2 | Week 6 | Week 12 | Week 24 | Week 36 | Week 52 | Early end of treatment |
| --- | --- | --- | --- | --- | --- | --- | --- | --- | --- |
| Informed consent | × |  |  |  |  |  |  |  |  |
| Specific medical history | × |  |  |  |  |  |  |  |  |
| General medical history | × |  |  |  |  |  |  |  |  |
| Focused history and physical examination | × | × | × | × | × | × | × | × | × |
| Weight | × | × | × | × | × | × | × | × | × |
| Laboratory^a^ | × | × | × | × | × | × | × | × | × |
| ECG | × | × | × | × | × | × | × | × | × |
| Registration | × |  |  |  |  |  |  |  |  |
| Randomization |  | × |  |  |  |  |  |  |  |
| Chest X-ray | × |  |  |  |  | × |  | × | × |
| X ray sacroiliac and whole spine | × |  |  |  |  | × |  | × | × |
| MRI sacroiliac joint & spine | × |  |  |  |  | × |  | × | × |
| Assessments |  |  |  |  |  |  |  |  |  |
| Efficacy | × | × | × | × | × | × | × | × | × |
| Safety | × | × | × | × | × | × | × | × | × |
| Concomitant medication |  |  |  |  |  |  |  |  |  |
| Biomarker analysis^b^ |  | × |  |  | × | × |  | × |  |

^a^ laboratory: hematology, blood chemistry, urinalysis, coagulation, ESR, CRP are required at all visits. Pregnancy test is required in female at childbearing age at screening.

^b^ Biomarker analysis: blood sample will be collected in patients who sign separate informed consent form for later biomarker and genomic analysis.

7.Assessments

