7.4 Radiographic assessments

The modified Stroke Ankylosing Spondylitis Score (mSASSS) was used to assess the structural change of AS patients. It assesses the anterior part of the cervical and lumbar spine (from the lower corner of T12 to the upper corner of S1 and from the lower corner of C2 to the upper cornor of T1) as follows: 0= normal; 1= erosion, sclerosis or squaring; 2= syndesmophytes; 3=bridging syndesmophytes (the total score ranges from 0 to 72).

8.Subject Withdrawal

Once a subject is randomized to investigational product, the subject’s vital status will be tracked for the duration of the study. Subjects may choose to discontinue use of investigational product at any time but full accountability at the end of the study is required of all subjects.

If a subject withdraws or discontinued for any reasons prior to last visit, e.g. to withdraw IFC, early withdraw from the study due to AE etc., an early end of treatment assessments listed in ”Early end of treatment” of the study flow chart at the last visit must be completed.

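### The only required pregnancy test is at screening; none is required at randomisation, during 52 weeks of treatment or before the repeat X-rays

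*Protocol*

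**What the plan says.** Footnote a to the timetable (Protocol section 6, Study procedures) sets two timings side by side. The routine laboratory items, "hematology, blood chemistry, urinalysis, coagulation, ESR, CRP are required at all visits". The pregnancy test has its own sentence and its own timing: "Pregnancy test is required in female at childbearing age at screening". The timetable has no separate pregnancy-test row, and section 7.2 (Safety Assessment) adds no test.

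Other parts of the protocol bear on this rule:

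- Section 4.2, first item, excludes "Pregnant women".
- Section 5.1: "Patient eligibility will be determined at the screening and baseline visits". The timetable marks randomisation at week 0.
- Section 4.1, item 5, obliges fertile women to use contraception "during the study and for at least 12 weeks after the last dose of test article".
- The timetable rows for chest X-ray and for "X ray sacroiliac and whole spine" are marked at screening, week 24, week 52 and early end of treatment. For a subject who leaves early, section 8 says the assessments in the early-end column "of the study flow chart at the last visit must be completed".

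**The concern.** The protocol itself treats pregnancy as incompatible with study treatment. It excludes pregnant women and asks for contraception throughout exposure and for a period after it. The test that supports the exclusion is nevertheless required once, before the second of the two visits at which eligibility is decided, and never again.

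An early pregnancy may not be evident from history and examination. A woman who conceives after the screening test can be randomised and dosed in full compliance with the schedule. A pregnancy that starts on treatment can be followed by more doses and by pelvic, spinal and chest X-rays before anyone knows of it. This is a matter of subject safety and has no bearing on power or error rates. It is also not something to leave to a statistical analysis plan, since the assessment schedule is protocol content and this protocol fixes it expressly.

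**Working it through.** The protocol gives no figure of its own to reproduce. The check is a reading of the schedule, a count from it, and a rough size under stated assumptions.

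**1. Is this a contradiction?** No. Inclusion criteria apply to patients who "meet all of the following criteria at screening or as specified", so a screening test is consistent with the exclusion, and footnote a sets a minimum that an investigator may exceed. The fault is a weak rule.

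**2. Required tests now** (timetable and footnote a):

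| Point in study | Required pregnancy tests |
| --- | --- |
| Screening | 1 |
| Week 0, before first dose | 0 |
| Weeks 2, 6, 12, 24, 36, 52 | 0 |
| Early end of treatment | 0 |

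So 0 of the 7 scheduled visits from week 0 to week 52 require a test.

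**3. X-rays without a recent test.** A completer has 2 repeat imaging visits with 2 X-ray rows each: 2 × 2 = 4 examinations. Her latest required test is at least 24 weeks old at the first visit and at least 52 weeks old at the second.

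**4. Gap from test to first dose.** The protocol states no interval between screening and week 0, so a gap can be derived only for some women. Consent must come before any study activity (11.1), and stopping current therapy may itself be the first study procedure (9.1). Under section 5.3, NSAIDs stop at least 7 days, and oral corticosteroids 4 weeks, before study drug. A woman tested before such a washout therefore has a test at least 1 week or 4 weeks old at her first dose. For other women no gap can be stated.

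**5. With tests at week 0, week 24, week 52 and early end:**

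- Completer: 3 added tests, 1 before the first dose and 2 after it.
- Early end before week 24: week 0 + early end = 2. After week 24: week 0 + week 24 + early end = 3.
- Untested intervals on treatment: 24 − 0 = 24 weeks and 52 − 24 = 28 weeks. The longest is 28, against 52 now.

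**6. Rough size.** The protocol does not give the number of women of childbearing age or a conception rate. Both are assumed here.

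| Quantity | Low | High |
| --- | --- | --- |
| Women of childbearing age, 10% to 40% of 150 | 0.10 × 150 = 15 | 0.40 × 150 = 60 |
| Added strips, 3 each | 15 × 3 = 45 | 60 × 3 = 180 |
| Pregnancies starting in 52 weeks, 1% to 5% per year | 15 × 0.01 = 0.15 | 60 × 0.05 = 3 |

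Section 8.1 replaces subjects withdrawn from product; each replacement woman adds at most 3 strips.

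**The case against.** The best defence is that nothing here is inconsistent. The screening test satisfies the criteria as worded, and investigators may test whenever they wish. Fertile women commit to contraception. History, examination, weight and safety assessment are marked at every visit, with at most 16 weeks between visits (week 36 to week 52), and the investigator may stop study product at any time. The pre-dose gap depends on when in screening the test is done. The pregnancy count rests on two assumed rates, spans a 20-fold range, and includes pregnancies that the added tests would not find any sooner.

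The remedy is also partial. The week 52 test comes at the end of treatment, so it protects that visit's X-rays and prevents essentially no dosing. Week 24 is then the only mid-treatment test, and a conception soon after week 0 or week 24 could still go untested for about half a year.

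Much of this stands. There is no contradiction, the pre-dose gap is conditional, the avoidable number is below the 0.15 to 3 and is not estimated, and the remedy narrows the untested period without closing it. What does not stand is the inference that the rule is adequate. The protocol did not rely on history and examination at screening, where it required a test as well. Contraception lowers the risk but does not confirm that a woman is not pregnant, and permission to test places no duty on a site.

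**Conclusion.** The concern holds, as a weak schedule rule that should be changed. Only one pregnancy test is required, at screening. None supports the exclusion at randomisation, none is required in 52 weeks of treatment, and none precedes a completer's 4 repeat X-ray examinations. These statements come from the protocol alone.

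The size in subjects is small and uncertain: about 0.15 to 3 pregnancies starting on treatment, entirely dependent on the assumed share of women and conception rate. The case therefore does not rest on that count. It rests on the exclusion the protocol already sets and on how little it costs to support it. The week 0 test has the clearest basis, because section 5.1 places eligibility at baseline too. Sample size, error rates and the primary analyses are unaffected.

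**What to change.** Replace the last sentence of footnote a with:

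> *A urine pregnancy test is required in women of childbearing age at screening, at week 0 before randomisation and dosing, and before the X-rays at week 24, week 52 and early end of treatment, using the urine already collected. A woman who tests positive at week 0 is not randomised. A later positive result is reviewed before any further dose or X-ray.*

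Testing at the other visits can stay optional. A sponsor who wants on-treatment intervals shorter than 24 and 28 weeks can make it mandatory at more of them, since urinalysis is already required at every visit.

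The cost is one footnote amendment and 3 strips per completer, at most 3 for a woman who ends early: about 45 to 180 strips under the assumptions above, plus those for replacements. Urine has to be taken before the X-rays at the imaging visits. A positive result may cost that woman an X-ray, and so a radiographic (mSASSS) reading under section 7.4. The two primary outcomes in section 2.2, SPARCC on MRI and ASAS20, do not use X-ray.

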The BASDAI is a six-item questionnaire used to assess the severity of five major symptoms of AS, including fatigue, spinal pain, peripheral arthritis, enthesitis, intensity of morning stiffness, and duration of morning stiffness using a 0-10 VAS scale. The Ankylosing Spondylitis Disease Activity Score (ASDAS) is used to assess disease activity in AS patients in five domains: total back pain (BASDAI item 2), patient global assessment, peripheral pain, and swelling (BASDAI item 3), duration of morning stiffness (BASDAI item 6), and CRP (mg/L). Four disease activity states were divided according to the ASDAS score cut-offs: <1.3 “inactive disease”, 1.3-2.1 “low disease activity”, 2.1-3.5 “moderate disease activity”, >3.5 “high disease activity”. For improvement scores, a major improvement (ASDAS MI) was defined as a decrease from baseline ≥2.0, and a clinically important improvement (ASDAS CII) was defined as a change ≥1.1 from baseline.

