9.4 Associated With the Use of the Drug

Not related
An adverse event which is not related to the use of the drug.

Doubtful
An adverse event for which an alternative explanation is more likely, e.g., concomitant drug(s), concomitant disease(s), or the relationship in time suggests that a causal relationship is unlikely.

Possible
An adverse event which might be due to the use of the drug. An alternative explanation, e.g., concomitant drug(s), concomitant disease(s), is inconclusive. The relationship in time is reasonable; therefore, the causal relationship cannot be excluded.

Probable
An adverse event which might be due to the use of the drug. The relationship in time is suggestive (e.g., confirmed by de-challenge). An alternative explanation is less likely, e.g., concomitant drug(s), concomitant disease(s).

Very likely
An adverse event which is listed as a possible adverse reaction and cannot be reasonably explained by an alternative explanation, e.g. concomitant drug(s), concomitant disease(s). The relationship in time is very suggestive (e.g., it is confirmed by de-challenge and re- challenge).

10.Data Analysis/Statistical Methods

The data will be analyzed by using ANOVA, those do not meet normal distribution will be analyzed by Kruskal-Wallis test. Statistical primary comparisons for SPARCC scores will be made using a repeated measures mixed model with terms for treatment, center and the corresponding baseline values as the covariates. Chi-square will be used for the comparison of proportion rate in different groups.

Analysis is performed for the ITT population and PP population. ITT population is defined as all randomly assigned subjects who received at least 1 dose of test article and had efficacy evaluation after baseline. PP population is defined as the cases that completed all treatment, had no protocol violation and completed all evaluation of study. The efficacy and safety analysis will be performed in the ITT population. And the primary efficacy analysis is also performed for the per-protocol (PP) population

11.Ethics

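### ASDAS low disease activity is defined as the band 1.3 to 2.1, which excludes patients who improve below 1.3; the comparison loses power and can, but need not, point the wrong way

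*Protocol*

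**What the plan says.** Section 2.2 of the Protocol includes "Ankylosing Spondylitis Disease Activity Score (ASDAS) remission and ASDAS low disease activity" among the secondary outcomes. Section 7.1 supplies the cut-offs: "Four disease activity states were divided according to the ASDAS score cut-offs: <1.3 “inactive disease”, 1.3-2.1 “low disease activity", then a moderate state at 2.1-3.5 and a high state above 3.5. These are presented as four divisions of one scale, so a score below 1.3 belongs to the inactive state and not to the low one. The Protocol gives no other definition of low disease activity, and section 7.1 defines no state called remission.

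For the analysis, section 10 says: "Chi-square will be used for the comparison of proportion rate in different groups". Section 3 fixes the size: "A total of 150 active AS patients will be randomized in a 1:1:1 ratio into the following three treatment groups", that is 150/3 = 50 per arm. Inclusion criterion [3] in section 4.1 uses "BASDAI≥4 or ASDAS score ≥2.1" as part of its definition of active disease, so there 2.1 counts as active.

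**The concern.** A response outcome should not be lost by improving further. Under the section 7.1 band, a patient who goes from 3.0 to 2.0 is in low disease activity, while one who goes from 3.0 to 1.0 is not. A treatment moves patients into the band from above and out of it from below, and the two flows offset each other in the proportion that the chi-square test compares.

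Two consequences follow. First, a real difference between arms can largely disappear. Second, if the more effective arm moves enough patients below 1.3, its low-disease-activity rate can be the lower one. In a trial whose question is whether the combination does better than either drug alone, a named outcome that can behave in this way is a poor basis for a statement about any arm.

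Two smaller defects sit in the same text. The value 2.1 belongs to both the low and the moderate band, and the remission outcome of section 2.2 has no definition under that name.

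**Working it through.** The Protocol gives no expected rate, power or alpha for this outcome, so there is no planned figure to reproduce. The check shows how the outcome behaves under stated assumptions.

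**Inputs from the Protocol:** cut-offs 1.3 and 2.1 (section 7.1); 50 per arm (section 3); chi-square on proportions (section 10).

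**Assumptions:** week-52 ASDAS normal with the same SD in both arms; SD 0.7, 0.9 or 1.1; five pairs of arm means; two-sided alpha 0.05; two arms compared at a time.

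**Formulas.** With mean m, SD s and Φ the standard normal distribution function:
- band as written: Φ((2.1 − m)/s) − Φ((1.3 − m)/s)
- cumulative: Φ((2.1 − m)/s)

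**Worked case, SD 0.9, means 1.4 (better) and 2.2 (worse):**
- Better arm: Φ(0.778) = 0.782 and Φ(−0.111) = 0.456, so the band is 32.6% and below 2.1 is 78.2%.
- Worse arm: Φ(−0.111) = 0.456 and Φ(−1.000) = 0.159, so the band is 29.7% and below 2.1 is 45.6%.
- A 32.6-point difference shrinks to 2.9 points. Power at 50 per arm (normal approximation) is about 5% for the band and 93% for <2.1.

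**Worked case, SD 0.9, means 1.2 and 2.0:**
- Better arm: Φ(1.000) = 0.841 and Φ(0.111) = 0.544, so the band is 29.7% and below 2.1 is 84.1%.
- Worse arm: Φ(0.111) = 0.544 and Φ(−0.778) = 0.218, so the band is 32.6% and below 2.1 is 54.4%.
- The better arm is 29.7 points ahead below 2.1 and 2.9 points behind in the band.

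**Range over all scenarios (better arm first; the three values are for SD 0.7, 0.9 and 1.1):**

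| Means | Band, % | Below 2.1, % | Reversed? |
| --- | --- | --- | --- |
| 1.8 vs 2.6 | 42.8 vs 20.6; 34.1 vs 21.5; 28.3 vs 20.6 | 66.6 vs 23.8; 63.1 vs 28.9; 60.7 vs 32.5 | no |
| 1.6 vs 2.4 | 42.8 vs 27.6; 34.1 vs 25.9; 28.3 vs 23.4 | 76.2 vs 33.4; 71.1 vs 36.9; 67.5 vs 39.3 | no |
| 1.4 vs 2.2 | 39.8 vs 34.4; 32.6 vs 29.7; 27.4 vs 25.7 | 84.1 vs 44.3; 78.2 vs 45.6; 73.8 vs 46.4 | no |
| 1.2 vs 2.0 | 34.4 vs 39.8; 29.7 vs 32.6; 25.7 vs 27.4 | 90.1 vs 55.7; 84.1 vs 54.4; 79.3 vs 53.6 | yes |
| 1.0 vs 2.0 | 27.6 vs 39.8; 25.9 vs 32.6; 23.4 vs 27.4 | 94.2 vs 55.7; 88.9 vs 54.4; 84.1 vs 53.6 | yes |

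In the three pairs without reversal, power for the band runs from about 4% to 67%, and for <2.1 from about 81% to nearly 100%. With equal SDs, the sign reverses when the better arm's mean lies further below the mid-band value of (1.3 + 2.1)/2 = 1.7 than the worse arm's mean lies above it.

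**Without the normal assumption.** Suppose that of 50 per arm the better arm has 25 inactive and 10 in the band, and the worse arm 8 and 15. The band rates are 10/50 = 20% and 15/50 = 30%. The rates below 2.1 are 35/50 = 70% and 23/50 = 46%.

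**The case against.** The strongest reply is that section 7.1 gives a classification, not a responder rule. No sentence says that patients below 1.3 are non-responders, and an analysis plan that is not shown could score the outcome as <2.1. It is true that no explicit rule is stated. But the Protocol does more than leave a detail open: it names the outcome and gives one definition, and a later plan using <2.1 would depart from it.

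A second reply is that patients below 1.3 would appear under the adjacent remission outcome, so the two rates could be added. This helps only if remission means the inactive state, which is the natural reading but is not stated. The low-disease-activity comparison would still be non-monotone when reported on its own. The change-based ASDAS measures in section 7.1, and ASAS20, BASDAI and BASFI, do not share the problem and would temper what a reader concludes.

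The third reply stands: the size depends on assumption. Three of the five mean pairs show no reversal. At 1.2 vs 2.0 the reversal is 5.4, 2.9 and 1.7 points for the three SDs, and only 1.0 vs 2.0 with SD 0.7 gives about 12. Even 20% vs 30% at 50 per arm is not significant: z = 0.10/√(0.25 × 0.75 × 2/50) = 1.15, p about 0.25.

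A reader might also infer that the shared value 2.1 lets patients enter the trial already in low disease activity. That follows from the boundary only for a score of exactly 2.1. Entry through BASDAI ≥4 allows a low baseline ASDAS wherever the band edges are drawn.

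**Conclusion.** The defect is real. The only definition of a named secondary outcome is a middle band that a patient leaves by improving. The main effect is loss of information: at SD 0.9 and means 1.4 vs 2.2, a 32.6-point difference becomes 2.9 points and power falls from about 93% to about 5%. The loss is smaller when both arms stay mostly above 1.3 (at SD 0.7 and means 1.8 vs 2.6, the band keeps about 67%).

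A reader might go further and infer that the better arm will show the lower rate, or that the trial would conclude it does worse. The documents do not support that. Reversal needs many patients below 1.3 in the better arm, the Protocol gives no expected ASDAS distribution, and the reversals computed here are mostly small. The means, SDs, normality and alpha are all assumptions. The outcome is secondary and one of several, so the change should be made, but the trial's primary conclusions do not depend on it.

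**What to change.** In sections 2.2 and 7.1:
- Define the secondary outcome ASDAS low disease activity as ASDAS <2.1 at the visit, including patients below 1.3.
- State that ASDAS remission means the inactive-disease state, ASDAS <1.3.
- Make the four states non-overlapping: <1.3; ≥1.3 to <2.1; ≥2.1 to ≤3.5; >3.5. This puts 2.1 in the higher band, consistent with the ≥2.1 activity cut-off in inclusion criterion [3].

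The four-state distribution per arm can be reported alongside, so that nothing shown by the band is lost. An ordinal comparison of the four states would also answer the concern.

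The cost is a wording change in two sections. No new data are needed, since the schedule in section 6 already has efficacy assessments and CRP at every visit. Any analysis plan should carry the same definitions.
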